### Estimation of sample size

2.6

This is a pilot study of the safety of RAH with MT in AIS patients with LVO of anterior circulation. There are no similar clinical studies like this, and thus, no information is available. According to Hertzog (16), 10–20 patients in each group were sufficient to assess the feasibility of a pilot study. Dobkin suggested that a minimum of 15 patients per group would be sufficient to decide whether a larger multicenter trial should be conducted (17). Therefore, we aimed to recruit 20 patients for each group in this study.

### Data management, monitoring, and quality assessment

2.7

The investigator will enter data accurately and promptly into the case report form based on the original observation records of subjects. Data will be entered using a dual-machine system and be verified twice for accuracy We will apply the multiple imputation method to process missing values. However, our primary focus during the implementation and data management stages of the clinical trials will be to prevent the occurrence of missing data as much as possible. We will strengthen data collection efforts and avoid any missing data cases to ensure our dataset’s integrity and effectiveness. Issues will be promptly reported to the monitor. Case report forms will be filed, stored in numbered order and archived.

The Luhe Hospital Research Expert Steering Committee and Ethics Committee will provide follow-up and supervision for the research project. The Luhe Hospital Research Expert Steering Committee will conduct quality control of the study, including planned enrollment, screened cases, currently enrolled cases, enrollment rate calculation, and follow-up management. The committee will analyze any problems and their causes and implement appropriate measures to manage the study. This study will follow standardized procedures for implementation to ensure the scientific rigor of the research and the accuracy, completeness, and authenticity of the data. These will include managing all aspects of the study, such as the informed consent process, screening and enrollment, randomization management, blinding, protocol adherence, management and recording of research instruments, data collection, project implementation, and management of project documents. The third-party quality control team will conduct regular on-site monitoring visits to hospitals to ensure strict adherence to all elements of the study protocol and accurate completion of study data. The project will be monitored and audited systematically, with a Quality Control report provided to the project leader. Additionally, 20% of the raw data will be spot-checked to examine data authenticity and completeness.

### Safety measurement

2.8

Due to the small number of participants, the short follow-up period, and the RAH applied to the skin surface of the splenic region, this study is considered relatively safe with few adverse reactions. Therefore, no interim analysis of safety will be performed. Special adverse events and serious adverse events will be closely monitored throughout the study. Any unfavorable medical event that occurs from the beginning of patient enrollment to follow-up, regardless of whether it is causally related to the trial treatment, will be judged as an adverse event. The investigators will evaluate these potential events according to their causality and severity. If they occur, they will be reported to the Ethics Committee of the Luhe Hospital and make amends.

### Statistical analyses

2.9

Data will be entered by persons not involved in the test, using double entry and setting up data range checks. Statistical analysis will be performed using SPSS version 19 (SPSS Inc., Chicago, IL, United States). Categorical variables will be expressed as percentages, and differences will be compared using the chi-square test; continuous variables conforming to normal distribution will be expressed as mean ± standard deviation, and differences will be compared using a *t*-test or ANOVA; continuous variables not all conforming to normal distribution will be expressed as median and upper and lower quartiles, and differences will be compared using rank sum test. Multi-factor linear regression or multi-factor Logistic regression analyses will be performed to control confounding factors according to the data type and outcome. *p* < 0.05 will be considered statistically significant.

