**Methods:**

This single-center, prospective, randomized controlled study (RCT) is proposed for AIS patients with anterior circulation large vessel occlusion (LVO). Subjects will be randomly assigned to either the control or intervention groups in a 1:1 ratio (*n* = 40). Participants allocated to the intervention group will receive RAH on the abdomen above the spleen prior to recanalization until 6 h after thrombectomy. All enrolled patients will receive standard stroke Guideline care. The main adverse events associated with RAH are focal cold intolerance and abdominal pain. The primary outcome will assess safety as it pertains to RAH application. The secondary outcomes include the efficacy of RAH on spleen, determined by spleen volumes, blood inflammatory factor (cells and cytokines), and on brain injury, determined by infarction volumes and poststroke functional outcomes.

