An increasing number of studies have demonstrated that splenic-derived inflammatory cells are an important source of inflammatory infiltration within brain tissue and that post-stroke activation of splenic inflammatory cells invade brain tissue, exacerbating the inflammatory and thus ischemia/reperfusion(I/R) injury (4–7). It was reported that splenic contraction occurs in some stroke patients within 24–48 h, followed by gradual recovery of splenic volume with clinical function improvement, according to clinical studies (8). Animal experiments further confirmed a significant reduction in spleen volume during the acute phase of stroke and the transit of splenocytes from the spleen to the ischemic area in the brain (8, 9). These studies suggested that activation and release of splenic inflammatory cells were the key factor in exacerbating cerebral ischemia/reperfusion injury. Inhibition of the reaction may block the inflammatory cascade response in the brain, leading to neuroprotection. Because of the detrimental effects of splenic inflammatory cells and factors, splenectomy is a widely studied means of splenic suppression. Splenectomy in a mouse model resulted in lower blood levels of multiple inflammatory factors than normal mice (9), reducing inflammatory cell infiltration in the brain and reducing brain infarct volume (10). Splenic pulse treatment suppressed the immune response in septic rats (11), and splenic irradiation similarly reduced infarct volume in mice (12). However, these approaches are largely prohibited in clinical practice since they cause irreversible suppression of the spleen (10, 13, 14). In the current study, the RAH above the spleen is hypothesized to prevent splenic contraction and reduce the release of splenic inflammatory cells and cytokines, which in turn may decrease brain infarct volume and improve long-term neurological function after stroke in humans. Furthermore, before this proposed clinical trial, our team investigated the efficacy of Remote Administration of Hypothermia (RAH) to the spleen in animal models of middle cerebral artery occlusion. During the experiment, the spleen temperature was reduced to 27°C, leading to reduced brain inflammatory response, decreased infarct volume, and improved functional prognosis (unpublished data). While our original pre-clinical animal data remains unpublished, the connection between splenic response and stroke injury, as well as protective effects, has been discussed in a recent study. In this study, it was demonstrated that diminished splenic response through inactivation or knockout of GPR55 improved neurological outcomes in a rodent model (15).

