**Figure 1 fig1:**
[figure not shown]
Flowchart of the study.

The criteria for recruitment are as follows: (1) Age of 18–80 years; (2) Patients with AIS; (3) LVO of the anterior circulation confirmed by computer tomography angiography (CTA), magnetic resonance angiography (MRI), or digital subtraction angiography (DSA); (4) Baseline National Institute of Health stroke scale (NIHSS) score ≥ 6 and Alberta Stroke Program Early CT Score (ASPECTS) >5; (5) Less than 24 h from stroke onset; (6) Acute occlusion of intracranial or extracranial segments of the anterior circulation vessels (thrombolysis in cerebral infarction score [TICI] classification 0-I); and (7) Informed consent of the participant or legally authorized representative (in cases where the patient’s decision-making ability is impaired due to a stroke) will be obtained.

The criteria for exclusion are as follows: (1) Spontaneous revascularization or rapid spontaneous improvement in neurological function (NIHSS<6 points); (2) Unsuccessful revascularization with MT (TICI = 0); (3) Rapid improvement in symptoms after revascularization; (4) Cranial imaging showing infarct area exceeding one-third of the area supplied by the middle cerebral artery pre-MT; (5) Pre-stroke modified Rankin Scale (mRS) >2; (6) Blood glucose <2.7 or > 22.2 mmol/L; (7) Laboratory evidence of coagulation dysfunction (platelet count <40 × 10^9^/L, APTT >50 s, or INR >3.0); (8) Pregnancy; (9) Splenic-related hematologic disorders, hypersplenism, or suppression; (10) Hypersensitivity of the skin, such as cold urticaria; (11) Obesity of patients (BMI ≥28/waist circumference > 90 cm); (12) Abdominal injury, surgical trauma and other factors intolerance to splenic hypothermia; (13) Patients enrolled within 3 months prior to this clinical trial or already enrolled in another clinical trial; (14) Failure to obtain informed consent; and (15) Patients with Splenectomy.

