#### Secondary outcomes (efficacy)

2.5.2

(1) Effect of RAH on Spleen: (a) spleen volume measurement: Spleen CT will be performed preoperatively, 24 h and 7 days after MT to determine the change in spleen volume. The area of each layer of the spleen will be calculated by circling the area with the Siemens CT workstation image software, and the overall spleen volume will be calculated by superimposing the layer thicknesses. An ultrasound of the spleen will be performed alternatively if the CT is not done. (b) comparison of blood inflammatory profiles, the changes in inflammatory cells and inflammatory factors (including leukocytes, neutrophils, lymphocytes, tumor necrosis factor, and interleukins 6, 8, and 10, etc.) before, at 24 h and 7 days after MT will be completed. (2) Effect of RAH on Brain: (a) infarct volume (MRI-DWI) between the two groups at 7 days after MT. Infarct volume measurement of cerebral infarcts will be performed by MRI-DWI with a Siemens Syngo workstation. The area of each infarcted layer will be automatically derived by circling the region of interest (ROI) on software of the workstation, and then the overall infarct volume is calculated by superimposing the layer thickness; (b) Intracranial hemorrhage will be classified as symptomatic intracranial hemorrhage based on the following: lethal intracranial hemorrhage and symptomatic intracranial hemorrhage defined as a postoperative CT showing an intracranial hemorrhagic lesion consistent with an NIHSS deterioration score of ≥4 according to the European-Australasian Acute Stroke Study (ECASS II) criteria; (c) comparison of neurological functional independence evaluation at 90-days for functional independence ratio (mRS 0–2 score) and 90-day mortality (mRS 6 score) between RAH and control groups will be determined.

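### Spleen volume and inflammatory markers have a pre-thrombectomy value, yet section 2.9 does not make baseline-adjusted regression the main comparison; doing so would sharpen the estimates at no extra data cost

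*Protocol article*

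**What the plan says.** All references are to the protocol article.

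- **Measurements (2.5.2, Secondary outcomes).** For the spleen: "Spleen CT will be performed preoperatively, 24 h and 7 days after MT to determine the change in spleen volume". Inflammatory cells and cytokines follow the same three time points, and they too are described as changes. So each of these outcomes has a baseline and two follow-up values.
- **Tests (2.9, Statistical analyses).** Continuous variables judged normal are summarised by mean and SD and compared by t-test or ANOVA. Those judged non-normal "will be expressed as median and upper and lower quartiles, and differences will be compared using rank sum test". The section does not say whether the value tested is the follow-up value or the change.
- **Regression (2.9, next sentence).** Multi-factor linear or logistic regression is planned to deal with confounding. The pre-MT value is not named as a covariate, and the section does not say whether the regression or the two-sample test is the main comparison.
- **Size (2.6, Estimation of sample size).** "we aimed to recruit 20 patients for each group in this study". This follows pilot rules of thumb, one of them that "10–20 patients in each group were sufficient to assess the feasibility of a pilot study". No effect size, SD or power is given.

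**The concern.** In a randomised trial of 40 patients, the pre-MT value of the same quantity is usually among the strongest available predictors of the follow-up value. A two-sample test on the follow-up value ignores it. A two-sample test on the change score uses it, but with a fixed slope of 1, which is best only when the correlation is very high. Regression estimates the slope and removes chance baseline imbalance from the treatment estimate.

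The regression in 2.9 could do this, but it is presented as a remedy for confounding. In a randomised comparison the main reason to adjust for baseline is precision, so the baseline value belongs in the main model by design.

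Letting normality choose the test has a further cost. With 20 per arm a normality check has little information, and the same marker could be reported as a mean difference at 24 h and as medians with a rank test at 7 days. Such results are hard to compare with each other or to carry into a later trial. That matters because the Conclusion says the findings will set parameters for future studies, and the Limitations say the splenic effect will be inferred from spleen volume and blood factors.

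**Working it through.** **The plan's own figure.** 2 × 20 = 40 agrees with the stated total. There is no power calculation to reproduce.

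**Inputs from the article.** n = 20 per arm (2.6), 1:1 allocation (Abstract and 2.3), significance level 0.05 (2.9; sidedness not stated).

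**Assumptions, not in the article.** Two-sided test; equal SD at baseline and follow-up; no missing data; baseline-to-follow-up correlation r between 0 and 0.9; illustrative treatment differences of 0.6 and 0.8 SD.

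**Formulas.** Variance of the treatment estimate, relative to a test on the follow-up value alone (= 1):
- Change score: 2(1 − r).
- ANCOVA: (1 − r²) × (N − 3)/(N − 4) = (1 − r²) × 37/36 with N = 40. The factor 37/36 = 1.028 is the price of estimating the slope.

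**Results.**

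| r | Change score | ANCOVA | ANCOVA ÷ change score |
|---|---|---|---|
| 0 | 2.00 | 1.000 × 37/36 = 1.03 | 0.51 |
| 0.3 | 1.40 | 0.91 × 37/36 = 0.94 | 0.67 |
| 0.5 | 1.00 | 0.75 × 37/36 = 0.77 | 0.77 |
| 0.7 | 0.60 | 0.51 × 37/36 = 0.52 | 0.87 |
| 0.9 | 0.20 | 0.19 × 37/36 = 0.20 | 0.98 |

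**Break-even points.**
- Against follow-up only, variances are equal where r² = 1/37, so r = 0.164. Allowing also for the lost degree of freedom, the detectable differences are equal at r = 0.169, or about 0.17. Below that ANCOVA loses at most 2.8% in variance.
- Against change scores, ANCOVA has the smaller detectable difference up to r of about 0.94. Beyond that the two are practically equal.

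**Detectable difference at 80% power, and power** (noncentral t; 38 df, or 37 df for ANCOVA):

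| r | Detectable difference in SD: follow-up / change / ANCOVA | Power at 0.8 SD: follow-up / change / ANCOVA |
|---|---|---|
| 0.3 | 0.91 / 1.08 / 0.88 | 69% / 55% / 72% |
| 0.5 | 0.91 / 0.91 / 0.80 | 69% / 69% / 80% |
| 0.7 | 0.91 / 0.70 / 0.66 | 69% / 89% / 93% |
| 0.9 | 0.91 / 0.41 / 0.40 | 69% / >99% / >99% |

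For a 0.6 SD difference at r = 0.5, power is 46% with follow-up only or change score, and 56% with ANCOVA.

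**The normality-gated procedure, simulated.** A Shapiro-Wilk check in each arm chose between t-test and rank sum test; ANCOVA was run on the log scale for log-normal data. At 0.8 SD and r = 0.5 (3,000 runs), power for follow-up gated / change gated / ANCOVA was:
- normal data: 71% / 71% / 82%;
- log-normal data: 67% / 69% / 81%.

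With no treatment effect (1,500 runs per setting, r from 0 to 0.9), rejection rates for all three lay between 3.8% and 6.1%, which is close to 5% given simulation error.

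**The case against.** **Adjustment is already planned.** Linear regression with treatment and the pre-MT value as terms is ANCOVA, and 2.9 does plan linear regression. A reader might infer from the named tests that the plan has no baseline adjustment, or that chance imbalance must stay in the estimate. The article does not support that. What stands is narrower: the baseline value is not given that role, and the regression is not made the main comparison.

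**This is detail for an SAP.** Covariate lists and model hierarchy for secondary outcomes are often left to a document not shown here, and their absence alone would be no finding. But 2.9 does not leave the method open: it states how continuous outcomes are compared and how the test is chosen. A better method for the same data is a comment on that stated choice.

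**Change is the natural comparator.** Section 2.5.2 words both outcome families as changes, so the two-sample tests may well be run on change scores. A reader might take the follow-up-only figures and conclude that ANCOVA is worth a near doubling of the sample at r = 0.7 (variance 52%). That would flatter the gain. Against change scores the saving is 13% at r = 0.7 and 2% at r = 0.9. It is larger at lower correlations: 23% at r = 0.5 and 33% at r = 0.3.

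**Splenic timing.** The Introduction says "splenic contraction occurs in some stroke patients within 24–48 h", while eligibility in 2.2 is "Less than 24 h from stroke onset". A reader might infer that baseline scans mix contracted and uncontracted spleens and so distort the change. The article does not establish this: on its figures the baseline could precede contraction, and randomisation balances onset time in expectation. It is not relied on here.

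**Infarct volume.** Section 2.5.2 gives only a 7-day volume, so there is no baseline volume to adjust for and the point does not extend to it.

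**Importance.** The primary outcome is safety and the trial is a pilot. That stands and limits the weight of the point.

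**Conclusion.** The point holds as an improvement in precision. For spleen volume and inflammatory markers, baseline-adjusted regression uses data already being collected and beats either two-sample approach at moderate correlations: about a quarter less variance than both at r = 0.5.

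The size depends on r, which the article does not give, and on which value the two-sample test would use, which 2.9 does not state. The advantage over follow-up only grows with r; the advantage over change scores shrinks with r. Because of the small loss at very low r, the gain is nearly but not strictly free.

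A reader might infer that the planned tests give invalid results. They do not: simulated type I error was near 5% throughout. Only the precision and consistency of secondary, preliminary-efficacy estimates are affected; the primary safety outcome is not touched. The figures further assume equal SDs at baseline and follow-up and complete data.

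**What to change.** In 2.9, or in the SAP if one exists:

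- State that the main analysis of spleen volume at 24 h and at 7 days is a linear regression of the follow-up value on treatment and the pre-MT value, reported as an adjusted difference with 95% CI.
- Use the same model for inflammatory cells and cytokines. For skewed markers use the log scale with the log baseline as covariate, reported as ratios with 95% CI. Fix the scale for each marker in advance and keep it the same at both time points.
- Drop the choice of test by normality for these outcomes, and keep rank sum tests as sensitivity analyses.
- Describe this regression as the main comparison, separate from any further confounder models.

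The cost is a few sentences and one estimated slope per model. No extra patients, visits or measurements are needed.

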### Patient and public involvement

2.10

Patients were not involved in the development of the study protocol and design, which were reviewed, revised and approved by the Research Expert Steering Committee of the Luhe Hospital and the Ethics Committee of the Luhe Hospital. The results of the study will be disseminated to the general public by means of seminars, public presentations and publication in peer-reviewed journals.

## Discussion

3

Revascularization strategies in acute ischemic stroke are becoming increasingly sophisticated, while successful revascularization gives ideal functional prognosis in only 46% of patients (1). Inflammation during reperfusion plays a significant role in I/R injury, hindering effective recanalization (18–20). Studies have identified splenic inflammatory cell activation and release after stroke as an important source of the central immune response (4, 18, 21). One recent study demonstrated that neurons in the central amygdala and paraventricular nucleus of the brain act directly over the spleen to regulate plasma cell production and that splenic denervation inhibits this process (22). The results suggested a regulatory role of brain-spleen circulation on adaptive immunity. Many preclinical studies proposed that activation and release of splenic inflammatory cells are closely related to cerebral I/R injury. Inhibition of these processes reduced brain inflammation, and thus attenuated the I/R injury (4, 5, 7, 9, 23, 24).

### Spleen-derived immune response and neuroprotective effects of inhibiting splenic inflammation

3.1

After a stroke, the brain and spleen communicate through various pathways, triggering immune cells to release cytokines and migrate to the affected area of the brain (25). These cytokines increase in the bloodstream around 24 h after the onset of ischemia. Levels of TNF-α, TNF-γ, IL-6, MCP-1, and IL-2 were significantly increased at 6 and 22 h after MCAO in mice with stroke injuries (26, 27). Besides, chemokines CCL2 and CCL3 attract monocytes and neutrophils after a stroke, with CCL2 peaking 2 days (28–30). Suppressing the splenic immune response after a stroke may be neuroprotective. Diminished splenic response by inactivation or knockout of GPR55 has been shown in rat models to improve neurological outcomes (15). Gu et. Al reveals external rat cooling to 30C with ETOH topically can result in neuroprotection and inhibit splenic contraction (31). Vagal nerve stimulation of the spleen has also been shown to reduce splenic inflammatory response (32).

Previous studies demonstrated that splenectomy prior to or immediately after a stroke significantly reduces infarct volume and inflammatory cell infiltration post-reperfusion in the MCAO model (10). Additionally, splenic pulsed therapy was found to suppress the immune response (11), non-surgical irradiation of the spleen in rats after MCAO reduced infarct volume (12) and inhibition a subpopulation of spleen-derived pro-inflammatory macrophages in mice resulted in a significant reduction in brain infarct volume (33).

